#### Retention Strategy

Participants will receive automated appointment reminders via the Nishauri platform and additional study reminders 1 week prior to their scheduled 8-month follow-up visit. For missed visits, trained study staff will attempt to contact participants by phone call or SMS text message to reschedule as soon as possible. If participants cannot be reached remotely, study staff will arrange an in-person follow-up at a safe and confidential location. Participants who relocate outside the study area will be contacted to facilitate follow-up data collection at an appropriate alternative site. These strategies are designed to minimize loss to follow-up and support sustained engagement with both the intervention and routine HIV care.

### Focus Group Discussions

#### Qualitative Data Collection

To complement the quantitative findings, 5 to 6 FGDs with approximately 6‐8 participants per group will be conducted in person by trained and qualified RAs and the principal investigator [name]. The FGDs will comprise 2‐3 with men living with HIV, 2 with health care providers (nurses, adherence counselors, or peer educators), and 1 with app developers. FGD sampling among men living with HIV will be stratified by factors such as age, ART adherence, and proportion of missed clinic visits (Table 1). We will invite 10 participants to each FGD and expect at least 6 to participate in each group. This sample size is expected to achieve thematic saturation in this study context, based on qualitative research standards [43] and was chosen based on guidelines, suggesting that 4‐6 FGDs are sufficient to reach thematic saturation in studies of similar scope and target populations [43-45]. This sampling strategy balances the need for rich qualitative data with feasibility considerations, allowing for in-depth exploration of implementation experiences across stakeholder groups. FGDs will continue until no new themes emerge, ensuring comprehensive coverage of barriers, facilitators, and contextual factors influencing the adoption, use, and sustainment of the Nishauri mHealth intervention.

To preserve the integrity of the data, most FGD participants will be different from those in the quantitative survey arm to reduce contamination, social desirability bias, and respondent fatigue. However, a limited number of individuals who participated in the pre- and poststudy may be included in FGDs to help explain emerging patterns in the data, as this study uses an explanatory mixed methods approach. Overlap will be explicitly tracked, and all analyses will account for repeated participation when interpreting themes, ensuring that qualitative findings complement, rather than double-count, quantitative data. Health care providers and app developers will also be purposively sampled to ensure representation of different implementation perspectives across the system.

The sampling plan and rationale for the FGDs is shown in Table 1. The FGD guides (Multimedia Appendix 2) have been organized thematically and include open-ended questions and follow-up probes to facilitate in-depth exploration of participants’ experiences with the intervention. We will explore contextual factors, including masculinity, stigma, and social norms, that influence the adoption, use, and sustainment of the Nishauri mHealth intervention. The FGDs will be audio-recorded using digital recorders and conducted in private settings to ensure confidentiality and adherence to ethical standards.

#### Qualitative Data Analysis

Audio recordings will be transcribed verbatim and translated into English and analyzed using Dedoose. We will use a thematic analysis approach combining deductive coding guided by Proctor’s implementation outcomes framework [36,37] with inductive coding to capture emergent themes not covered by the framework. Descriptive statistics will summarize FGD participant demographics. Narrative summaries, tables, diagrams, and cross-case comparisons will be used to deepen interpretation. Triangulation with app analytics (eg, proportion of missed visits and use metrics) and member checking will enhance credibility. This study uses an explanatory sequential mixed methods design, using quantitative data to assess intervention uptake and outcomes, followed by qualitative inquiry to explain how factors like masculine norms, stigma, and system-level challenges influence these patterns. Qualitative findings will be integrated with application data from the Nishauri dashboard to uncover underlying mechanisms and contextual factors shaping implementation outcomes. Standard operating procedures will guide FGD facilitation, qualitative data handling, and analysis.

### Dissemination Plan

Study findings will be shared with participants, health care providers, Homa Bay County Ministry of Health officials, and other key stakeholders. Results will be disseminated through presentations at local and international conferences focused on HIV prevention, treatment, and behavioral medicine, as well as through publication in peer-reviewed journals. The study team has established an authorship agreement outlining contributions to primary and secondary publications. Participants’ identities will remain confidential and will not appear in any reports or publications. Direct feedback will also be provided to research participants and community partners to ensure inclusive and transparent communication of the findings.

### Ethical Considerations

This study will be conducted in accordance with the ethical principles of the Belmont Report—respect for persons, beneficence, and justice. Ethics approval was obtained from the Maseno University Scientific Ethical Review Committee (MSU/DRPI/MUSERC/01502/25), which serves as the primary institutional review board. All study materials, including the study protocol, data collection tools, and any protocol amendments, will be submitted to the institutional review board for review and approval prior to implementation. In addition, administrative and institutional approvals were obtained from the National Commission on Science, Technology and Innovation, Homa Bay County—Department of Health, the participating health facilities (Mbita, Ndhiwa, Ogongo, and Pala subcounty hospitals), and the University of California, San Francisco Department of Epidemiology and Biostatistics. All study staff will complete training in human subjects’ protection and Good Clinical Practice prior to study initiation. Written informed consent will be obtained by trained RAs before any study procedures are conducted. Consent forms will be available in English, Dholuo, and Swahili, and participants will choose their preferred language. Literate participants will read and sign the form; those with limited literacy will have the form read aloud in the presence of an impartial witness who will document the consent accordingly. All participants will receive a copy of the signed consent form, or if deemed unsafe to keep, may store it at the clinic and receive a contact slip for future reference. Participants will be reimbursed Ksh 300 (US $2.32) for their time. Strict confidentiality measures will be observed, given the sensitivity of HIV-related data. Personal identifiers will be anonymized or pseudonymized, and all data will be stored in secure, encrypted systems accessible only to authorized, trained personnel. Participants will be informed of confidentiality protections during the consent process. Hard copies of study documents will be stored securely for 5 years before being shredded; electronic and audio files will be permanently deleted at that time.

## Results

The study obtained institutional review board approval on July 28, 2025. Baseline data collection began on September 8, 2025, and has been completed in 3 health facilities and is anticipated to end by January 31, 2026. A total of 307 men living with HIV were recruited across the 4 clinics for the pre- and postquantitative assessment. Follow-up and app use monitoring are ongoing in the first facility. Follow-up data collection is expected to be completed in August 2026. Analysis is projected to be concluded in the third quarter of 2026, and the results will be submitted for publication at the end of 2026. Findings are anticipated to inform gender-responsive adaptations of digital health strategies and guide policy recommendations for scaling mHealth interventions for men living with HIV in Kenya.

## Discussion

### Principal Findings

This study is guided by a conceptual framework integrating Proctor’s implementation outcomes framework, TAM, and the masculinity model (Figure 3). It is designed to generate evidence on the implementation and impact of the Nishauri mHealth intervention on HIV care and treatment among men living with HIV in Homa Bay County, Kenya. With this model guiding data collection and analysis, we anticipate findings that will address critical gaps in understanding how mHealth tools perform in resource-constrained, gendered contexts.

By identifying both individual- and system-level factors that influence the adoption, use, and sustainment of the Nishauri platform, this study will generate valuable insights into the dynamic interplay between client- and organizational-level implementation outcomes. Barriers such as limited digital literacy, stigma, poor network coverage, and workflow integration challenges, as well as facilitators like ease of use, perceived usefulness, provider support, and trust in the health system, will be explored in depth. These findings will inform the development of gender-responsive, culturally grounded adaptations to Nishauri as well as other digital health strategies aimed at improving long-term health outcomes for men living with HIV in Kenya and advancing national efforts to close gender gaps in HIV care.

We hypothesize that there will be measurable improvements in HIV service outcomes, particularly ART adherence and clinic retention, among men exposed to the intervention, compared to control periods within the stepped-wedge design. These outcomes will be interpreted in light of confounding variables, such as age, education, and stigma, and supported by app analytics and chart review data. Furthermore, the client outcome of VLS will offer a critical downstream indicator of the intervention’s potential clinical impact.

This study will contribute critical insights into how masculine norms shape the implementation and impact of digital health tools for HIV care. By unpacking how behavioral constructs such as autonomy, stoicism, and fear of vulnerability influence engagement with mHealth interventions, the findings will inform the development of more gender-responsive and contextually grounded digital strategies. These insights have the potential to guide national policies and programs aiming to close gender gaps in HIV care by tailoring interventions to the unique needs and experiences of men.

By integrating implementation science and gender theory within a mixed methods design, this study will generate a nuanced understanding of individual- and system-level factors influencing the success of mHealth tools among men in HIV care. While the findings may be context-specific to Homa Bay County, they offer valuable insights to inform the design and scale-up of culturally relevant, gender-sensitive digital health strategies in Kenya and similar low-resource settings. Future research should build on these results to codevelop scalable interventions and policy frameworks that support sustainable integration into routine HIV care for men.

### Strengths

This study has several strengths, including its use of a stepped-wedge design within real-world public health settings, enhancing both rigor and relevance. By focusing on men, an underserved population in HIV care, and guided by Proctor’s implementation outcomes framework, the study offers a structured analysis of adoption, use, and sustainability. The explanatory sequential mixed methods approach, combined with mHealth app data, allows for deep insights into both outcomes and underlying mechanisms. Additionally, the study’s gender-informed lens and alignment with national HIV priorities position it to generate policy-relevant evidence for more effective and equitable digital health interventions.

### Limitations

While this study uses a stepped-wedge cluster randomized design, several limitations should be noted. First, the number of clusters (health facilities) is small, which may limit statistical power and the ability to control for facility-level confounding. The small number of clusters limits the precision with which facility-level confounders can be modeled and reduces degrees of freedom for estimating random effects. As a result, adjustment for cluster-level confounding is restricted to a limited set of prespecified facility characteristics (eg, size and urban-rural setting), and residual confounding at the facility level cannot be entirely ruled out. To mitigate this limitation, analyses will include fixed effects for time, intention-to-treat estimation, and triangulation with qualitative data to support interpretation of observed effects. Second, reliance on self-reported survey measures for some implementation outcomes (eg, acceptability and adherence) and masculinity factors may introduce recall or social desirability bias. Third, inclusion criteria requiring smartphone or tablet ownership may exclude more men from resource-limited countries, potentially limiting the generalizability of findings. Finally, variations in how the intervention is implemented across facilities—due to staffing, infrastructure, or engagement differences—may influence observed effects. Despite these limitations, the study’s mixed methods approach and triangulation of data sources will enhance the robustness and contextual relevance of the findings.

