**Methods:**

We will use a mixed methods design combining a stepped-wedge cluster approach and a pre- and postimplementation assessment across 4 health facilities in Homa Bay County, Kenya. Approximately 347 men receiving HIV treatment who own a smartphone will be enrolled. The stepped-wedge design will sequentially introduce the intervention across the 4 facilities in 2-month intervals following baseline assessments, allowing each site to serve as its own control. Surveys will collect data on sociodemographics, masculinity, intervention acceptability and uptake, and HIV clinical outcomes using validated measures. Intervention effects on pre- and postbinary outcomes will be assessed using the McNemar test, while generalized estimating equations (*α*=.05; *β*=.2; 95% CI) will account for clustering and repeated measures in the stepped-wedge analysis. Focus group discussions (n=5-6) will be conducted with men living with HIV, health care providers, and app developers to explore barriers and facilitators of implementation and adoption. Focus group discussions will be audio-recorded, transcribed, coded, and analyzed thematically.

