**Conclusions:**

This trial will use a stepped-wedge design to evaluate the implementation and effects of the Nishauri mHealth intervention on antiretroviral therapy adherence and clinic attendance among men in Homa Bay County. By examining both clinical outcomes and the influence of masculine norms on intervention uptake, it will provide robust evidence on the effectiveness of mHealth strategies tailored for men in low-resource, high–HIV-burden settings. Findings will inform the design, scalability, and optimization of similar interventions by identifying key implementation barriers and facilitators.

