**Figure 1. F1:**
[figure not shown]
Study Schema. FGD: focus group discussion; HCP: healthcare providers.

**Table 1. T1:** Focus group discussion (FGD) sampling plan or rationale.

Group	FGDs, n	Participants per FGD, n	Total participants, n	Plan or rationale
Men living with HIV	2‐3	6‐8	12‐24	Stratified by age, missed visits, antiretroviral therapy adherence, and intervention adoption.
Health care providers	2	6‐8	12‐16	Grouped by facility or role (eg, nurse vs adherence counselor). County or subcounty officials to provide valuable insight into policy, scale-up, and sustainability.
App developers	1	4‐6	4‐6	Being a homogeneous group, 1 FGD session should suffice.

After baseline data collection is completed, a standardized readiness assessment will be conducted across the 4 facilities to determine the procedure of the phased intervention rollout. We will leverage a partnership with the Palladium Group (the app developers) to access backend use data from the Nishauri app, providing detailed insights into how different app functions are used in real-world settings. This mixed methods design will enable both within- and between-facility comparisons, offering a nuanced understanding of how implementation processes and gendered experiences shape the intervention’s effectiveness among men. This study protocol was developed and reported in accordance with the SPIRIT (Standard Protocol Items: Recommendations for Interventional Trials) 2013 guidelines (Checklist 1).

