### Stepped-Wedge Intervention Approach

#### Strategy

A stepped-wedge design was chosen to allow all facilities to receive the intervention, accommodate phased training and app deployment, minimize contamination between sites, and enable within-facility comparisons over time while controlling for secular trends. The 4 CCCs will undergo a standardized readiness assessment, and phased implementation of the intervention will proceed in sequence according to facility readiness, with sites transitioning from standard care to the mHealth intervention arm over an 8-month period. The phased rollout will occur at 2-month intervals across the 4 participating facilities, resulting in 5 study periods (1 baseline and 4 intervention steps) over approximately 8 months. The 2-month interval was selected to align with routine HIV clinic visit schedules in Kenya [18], allow sufficient time for provider training and participant onboarding, and permit stabilization of app engagement before subsequent facility transitions. This interval is consistent with stepped-wedge evaluations of health service and digital interventions [42] and supports the detection of short-term changes in missed clinic visits and adherence behaviors while accounting for secular trends.

We acknowledge that the 2-month step length is relatively short and may limit detection of longer-term intervention effects within each wedge; however, this interval was selected for programmatic feasibility and alignment with routine HIV care cycles, and outcome measures were therefore chosen to capture proximal, short-term indicators of engagement and retention.

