#### Stepped-Wedge Analysis

We will analyze intervention effects using intention-to-treat principles and generalized linear mixed models appropriate to each outcome. Models will include a fixed effect for time period (step) to account for secular trends, a fixed indicator for intervention exposure during each step (within-cluster), and random intercepts for clusters (facilities) to account for within-cluster correlation. Where appropriate, we will include random slopes for time if supported by the data. Covariates prespecified for adjustment include patient-level baseline characteristics (age, gender, income, education, and stigma) and facility-level covariates (facility size and urban or rural). We will use robust SEs (cluster-robust SEs) to ensure valid inference with a limited number of clusters. Additional sensitivity analyses will include per-protocol analyses and models testing for time-by-intervention interaction to explore whether effect sizes change across steps. Primary inference will be 2-sided with *α*=.05. Analyses will be performed in Stata (StataCorp LLC; xtmelogit/xtmixed), and code will be archived with the study repository for reproducibility.

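### The Limitations section calls the design cluster randomized, but the facility order follows a readiness assessment and no random allocation is described

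*Protocol article*

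**What the plan says.** The Limitations section opens with the words "While this study uses a stepped-wedge cluster randomized design, several limitations should be noted". Two places in the Methods say how the order of the four facilities is set. Study Design says that, after baseline data collection, "a standardized readiness assessment will be conducted across the 4 facilities to determine the procedure of the phased intervention rollout". The Strategy subsection of the Stepped-Wedge Intervention Approach says that "phased implementation of the intervention will proceed in sequence according to facility readiness".

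Elsewhere the design is named without any reference to randomization. The Abstract's Methods, for example, state: "We will use a mixed methods design combining a stepped-wedge cluster approach and a pre- and postimplementation assessment across 4 health facilities". In the Stepped-Wedge Analysis subsection the word random is attached only to intercepts and slopes.

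Two statements bear on how the result will be read. The Abstract's Conclusions promise that "it will provide robust evidence on the effectiveness of mHealth strategies tailored for men". The analysis subsection states: "We will analyze intervention effects using intention-to-treat principles and generalized linear mixed models appropriate to each outcome". The Limitations section concedes that "residual confounding at the facility level cannot be entirely ruled out", but presents this as a consequence of having few clusters.

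**The concern.** A facility order cannot be both randomized and determined by a readiness assessment. The label matters because it tells readers, risk-of-bias assessors and evidence synthesists whether the switch date is independent of facility conditions by design or only by assumption.

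Under a readiness order, the switch date may be related to features of a facility that also affect missed appointments. Period effects remove a secular trend common to all facilities, and the facility intercept removes nearly all of a stable difference between facilities. Neither removes a facility-specific change that happens to occur around the switch. Intention-to-treat analysis does not help, because it preserves a randomized comparison and none is described here.

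The one caveat on confounding does not tell the reader that the order was chosen on a facility characteristic.

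**Working it through.** **1. Statements on allocation, side by side.**

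| Place | How the order is set |
|---|---|
| Limitations | Labelled cluster randomized |
| Study Design | Readiness assessment after baseline determines the rollout |
| Strategy | In sequence according to readiness |
| Abstract (Methods) | Stepped-wedge cluster approach, randomization not mentioned |
| Stepped-Wedge Analysis | Random refers to model effects only |

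The two passages that describe a procedure agree with each other. The single label contradicts both.

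**2. The plan's own power figure, to confirm the model used below.** Inputs from Power Estimation for Stepped Wedge Analysis: facility sizes 758, 294, 598 and 249 (total 1899), 5 periods, baseline proportion 0.20, odds ratio 0.75, intracluster correlation 0.02, α = .05. The two-sided test is from Stepped-Wedge Analysis.

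- Baseline odds: 0.20/0.80 = 0.25. Intervention odds: 0.75 × 0.25 = 0.1875. Proportion: 0.1875/1.1875 = 0.158. Target effect: 20.0% − 15.8% = 4.2 points.
- Hussey-Hughes variance on the risk-difference scale, one facility crossing per step, all 1899 men observed in every period (assumption): power averages 0.82 over the 4! = 24 possible orders, range 0.80 to 0.84. This agrees with the stated ~80%.
- The order moves power by only 4 to 5 points. The readiness order is therefore a question of validity, not of power.

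**3. What a change near the switch does to the estimate.** In a linear model with facility and period effects, the treatment estimate is a weighted sum of the 20 facility-period means. Summing the weights by time since the switch and averaging over the 24 orders gives:

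| Period after switch | 1st | 2nd | 3rd | 4th |
|---|---|---|---|---|
| Total weight | 1.00 | 0.30 | −0.10 | −0.20 |

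These sum to 1.00. The first-period weight lies between 0.94 and 1.07 in every order. The last period before each switch carries an equal and opposite total weight.

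Now assume that every facility has a temporary 2-point improvement in missed visits unrelated to the app. The 2 points and the timing are assumptions; the document gives neither.

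| When the improvement falls | Bias in the estimate |
|---|---|
| Switch period only | 2 × 1.00 = about 2 points in favour of the app |
| Switch period and the one before | 2 × (1.00 − 1.00) = 0 |
| Period before the switch only | 2 × (−1.00) = about 2 points against the app |

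Against a target of 4.2 points, 2/4.2 = 48%, in either direction.

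**4. Other routes.**

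- *Linear trends that differ by rank in the order.* With an assumed 0.5 point per rank per period, the bias averages 0 over the 24 orders under facility fixed effects. A single order can give about ±0.3 points.
- *Stable facility differences.* With an assumed 2 points per rank (a 6-point spread over four facilities), the random-intercept model leaks about 0.14 points into the effect, or about 0.05 once size and urban or rural setting are included. Facility fixed effects leak none.

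**The case against.** The case against making much of this is substantial.

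- The word randomized is applied to the study once, in a subordinate clause. The Strategy subsection states the readiness order openly, and the aims speak of potential effects.
- The Limitations section already concedes residual facility-level confounding. It separately warns that differences in staffing, infrastructure or engagement may influence the observed effects.
- A within-facility comparison adjusted for period remains useful quasi-experimental evidence.

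All of this stands, and it limits the required change to wording. It does not make the label true, and it does not supply the missing link between the order and confounding.

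A reader might go further and infer that the order inflates the apparent benefit, by as much as half the target effect. The document does not support that. It requires each facility to be switched at its own temporary best, whereas Study Design describes one assessment after baseline, with the remaining facilities following at 2-month intervals. The same assumed 2 points can equally favour the app, cancel out, or count against it.

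A reader might also infer that the random intercept leaves stable facility differences largely uncorrected. The leak is about 0.1 point, so that is not a material defect.

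Finally, the document does not say what the readiness assessment contains. That it reflects staffing or engagement is plausible but not stated.

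**Conclusion.** The label is wrong as written. The procedure described is a non-randomized stepped wedge ordered by readiness, and the Limitations section does not name that ordering as a source of confounding. This rests on the text alone and needs no assumption, except that the parts of the article not shown contain no description of a random draw.

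The bias is undetermined in both size and sign. For an assumed 2-point transient change it ranges from about 2 points in favour of the app, through 0, to about 2 points against it, compared with a target effect of 4.2 points. Those figures rest on a linear approximation to the planned logistic model, with all men observed in every period.

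Correcting the wording is necessary because it changes what the trial can claim. The document does not establish that the estimate will be biased.

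**What to change.** **Required, text only:**

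- In Limitations, replace the words cluster randomized with non-randomized, readiness-ordered.
- In the same section, state that facilities were ordered by readiness, that the switch date may therefore be related to facility conditions, and that this is a source of confounding separate from the small number of clusters.
- In the Abstract's Conclusions, replace the promise of robust evidence on effectiveness with wording suited to quasi-experimental evidence.

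**Optional, low cost:**

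- Fit facility fixed effects, as a sensitivity analysis or in place of random intercepts plus size and urban or rural setting. The gain is small (about 0.1 point), and so is the loss of power (about 0.5 percentage points in the model above).
- Show missed-visit levels and trends by facility before the switch, taken from the routine records the study already uses. This is the most direct evidence available to a reader on whether conditions were changing as facilities switched.
- Draw the order of the facilities not yet switched at random, if still feasible. The Results section reports: "Follow-up and app use monitoring are ongoing in the first facility". At most three facilities could then be drawn, giving 3! = 6 orders, and the trial as a whole would still not be randomized.
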